
### Standard of care for participants

This trial is pragmatic in design and, apart from random allocation of treatment option and participant completion of diaries and questionnaires; participant care will follow standard pathways in participating secondary care NHS sites. Both prophylactic antibiotic and methenamine hippurate are licensed and approved for routine NHS use. We will ensure that all participants have access as desired to the use of other measures to reduce the risk of UTI such as adequate fluid intake, avoidance of constipation, and, for post-menopausal women, vaginally administered oestrogen supplements. We will also ensure that all participants are informed regarding the possible benefit of other alternative options including cranberry extract. Participants in both trial groups may receive discrete courses of antibiotics as decided by the responsible clinician for symptomatic UTI. Use of all these adjunctive treatments will be recorded on CRFs.

### Concomitant medication

It is the responsibility of the prescribing clinician to check for interactions between trial drugs and other medications.

### Baseline

The following procedures will be undertaken at the baseline visit, prior to randomisation, but after the participant has given informed consent:Demographic review/document eligibility including UTI details (stratify UTI frequency for randomisation)Pre/post menopause (stratify for randomisation)Document adjunctive treatments, e.g. cranberry/ oestrogens/ D-mannose/probioticseGFR and LFTs, plus optional sample for storage and DNA analysisHealth Resource Use QuestionnaireEQ5D-5 LMid-stream specimen of urine (MSU) for microscopy and culture plus MSU for central laboratoryOptional perineal swab for culture for the presence of *E.coli* (central laboratory only)

### Randomisation

Participants will be randomised onto the study as close to the time of consent as possible. Participants who are undertaking the 3-month washout will consent to the study prior to undertaking the washout but will not be randomised or complete the other baseline measures until this has been completed. Their continued consent and eligibility will be confirmed at this point.

### Post randomisation

Post randomisation there will be a discussion of the trial documentation with the participant and the trial medication will be prescribed (either methenamine hippurate or antibiotic prophylaxis). Site staff will also go through the instructions for what to do if the participant experiences a UTI and how to complete the UTI record and take and send the associated samples.

### Once-monthly telephone calls

A member of the trial team will contact the participant once monthly (when they are not attending a visit in person) to check compliance, any concerns of the participant and tolerance of their allocated investigational medicinal product (IMP).

### Face-to-face appointments at 3, 6, 9, 12, 15 and 18 months

Participants will attend a face-to-face appointment every 3 months. At this appointment the following will be completed:UTI diary reviewCompletion of CRF by trial staffMSU for microscopy and culture (plus MSU for central laboratory)Optional perineal swab (central laboratory only at 6, 12 and 18 months)eGFR and LFTs blood testsPrescription for trial medication (3, 6 and 9 months only)

### At the time of UTI

At the time of the participant experiencing a UTI, they will complete and return:Participant UTI recordEQ5D 5 LMSU for culture and microscopy (plus MSU for central laboratory)Trial staff to complete report alert after telephone call from participant

### Questionnaires sent directly to participants

A number of questionnaires will be sent directly to participants from the central team at the Newcastle Clinical Trials Unit. These are as follows:UTI Symptom QuestionnaireEQ5D 5 LHealth Resource Use QuestionnaireTQSM

### Microbiological methods

MSU samples will be sent to the central reference laboratory in universal containers pre-loaded with boric acid at a concentration of 18 g/L (International Scientific Supplies Ltd., Bradford, UK). Microscopy and semi-quantitative culture of mid-stream specimens of urine will be carried out in accordance with the UK Standards for Microbiology Investigations [26]. The presence of up to two isolates at ≥1 × 10^5^ cfu/mL or one isolate at ≥1 × 10^4^ cfu/mL will be reported, while bacterial counts of ≤10^3^ cfu/mL and mixed cultures of three isolates or more will be regarded as not significant. Presumptive identification will be confirmed by matrix-assisted laser desorption ionisation-time of flight mass spectrometry, MALDI-TOF (Bruker microflex, Coventry, UK). Disc diffusion susceptibility testing against a panel of antimicrobial agents will be carried out using Mueller-Hinton agar (Oxoid Limited, Basingstoke, UK) in accordance with the methods outlined by The European Committee on Antimicrobial Susceptibility Testing (EUCAST) [27]. For *E. coli* isolates, susceptibility testing will be carried out in triplicate. Perianal swabs will be inoculated onto ChromID® CPS® Elite media (bioMérieux, Basingstoke, UK) and examined for the presence of *E. coli* after overnight incubation in room air at 37 °C. As above, antimicrobial susceptibility testing will be carried out in triplicate for *E. coli* strains using EUCAST disc diffusion methodology [27].

### Subject withdrawal

Participants have the right to withdraw from the trial at any time without having to give a reason. Investigator sites should try to ascertain the reason for withdrawal and document this reason within the CRF and participant’s medical notes.

The investigator may discontinue a participant from the trial at any time if the investigator considers it necessary for any reason including:PregnancyParticipant withdrawal of consentInvestigator’s discretion that it is in the best interest of the participant to withdrawAn adverse event (AE) that renders the participant unable to continue in the trialTermination of the clinical trial by the sponsor

Participants who withdraw from the trial will not be replaced. There are three withdrawal options:Withdrawing completely (i.e. withdrawal from allocated treatment and provision of follow-up data, including follow-up through patient healthcare records)Withdrawing from the allocated treatment (moving to the alternative treatment arm) in the trial but allowing continued full follow up (including questionnaires) and review by research team of healthcare recordsWithdrawing from the allocated treatment in the trial and the active follow-up but allowing the research team to follow-up through healthcare records

A proportion of participants who discontinue participation in the study will be invited to take part in the qualitative interviews as it is important to understand why some participants withdraw from the trial.

### Definition of the end of study

The definition of the end of the trial will be the last participant’s last follow-up visit at 18 months post randomisation. An end-of-trial declaration will be submitted to the REC and MHRA.

### Source of bias

Selection bias will be minimised by including all adult female patients with recurrent uncomplicated UTI as eligible participants. We have deliberately set few exclusion criteria to enable the findings of this study to be generalisable. Both treatments are licensed for this condition, exhibit a low side-effect profile. Target population and sample size and have little interaction with other common medications, which limits absolute contra-indications to either therapy. We will stratify randomisation on the basis of number of UTIs (more than four episodes per year vs four or more episodes per year) and menopausal state (pre-menopausal vs menopausal/post-menopausal) of the participants to ensure equivalent proportions of these groups at differential risk in both arms.

Eligible patients and their responsible clinicians will need to be sufficiently uncertain of the optimum treatment for rUTI to allow randomisation. The ‘Background and Rationale’ section (sections ‘1 and 2’) of this document sets out the existing evidence for both treatments and describes Level-1 evidence to support the use of both prophylactic antibiotics and methenamine hippurate. Similar reductions in the frequency of episodes of UTI are reported for both treatments and clinicians should, therefore, have equipoise based on these data. This should ensure that any selection bias in terms of characteristics of rUTI sufferers put forward and willing to be randomised compared with those who are eligible but not willing to participate is minimised. We will keep an anonymised screening log at each centre listing demographic and clinical characteristics and reasons for declining randomisation (if offered) and compare this group with those entering and those completing the trial. Secondly the characteristics of participants who switch treatment arm during the 12-month treatment period may differ from those completing the allocated strategy. We will address this by comparison of demographic data and QoL scores between these groups measured at baseline prior to randomisation and following treatment.

### Data handling and record keeping

Data will be collected using CRFs, participant-completed questionnaires, UTI diaries and information retrieved from medical notes. Data will be entered remotely at each site into the secure validated clinical data management system Elsevier’s MACRO by the local investigator or another member of the site research team with delegated responsibility for this activity. A site delegation log of the study site personnel and their delegated study activities will be kept in the Investigator Site File (ISF) throughout the duration of the study. CRFs, participant-completed questionnaires and UTI diaries which are entered into eCRFs in the MACRO database at a later date will be classed as source documentation. Results of urine and perineal swab analysis will be uploaded securely into the MACRO database by the database manager from reports produced by the central laboratory. Data will be handled, computerised and stored in accordance with the Data Protection Act 1998 and the General Data Protection Regulation (GDPR) from 25 May 2018. Under the trial participant consent, identifiable data will be stored in a separate, password-protected database within Newcastle Clinical Trials Unit (NCTU), with access limited to those members of the trial team responsible for the preparation and sending of follow-up questionnaires and logging their return. This database will also be used to maintain a record of each participant’s preferred method of communication with the trial team, and to ensure that trial correspondence is sent to each participant using their preferred mode of delivery. The quality and retention of study data will be the responsibility of NCTU. All study data will be retained in accordance with the latest Directive on Good Clinical Practice (GCP) and local policy.

Questionnaires returned by post to the trial management office in Newcastle will be entered by the trial administrative team at NCTU. The NCTU trial ,management team in collaboration with the database manager will work closely with local site research teams to ensure that the data are as complete and accurate as possible. The NCTU trial management team will be responsible for chasing missing data with sites. Two reminders will be sent to participants to prompt return of questionnaires. Extensive range and consistency checks are done to enhance the quality of the data.

### Access to data and data security

Caldicott approval for use, transfer and storage of participant identifiable information will be obtained at each site.

All research data will be kept in accordance with Newcastle University’s information security policy (http://www.ncl.ac.uk/itservice/policies/). Newcastle University maintains a series of regular backups and off-site mirror servers to ensure continuity and disaster recovery.

Elsevier’s MACRO database is an electronic data capture system which complies with the requirements of regulatory bodies and maintains an audit trail of any changes to the data. All data stored in MACRO benefit from Elsevier’s hosting service in collaboration with Rackspace which features redundancy and backup measures in case of disaster. Users have password-limited access to the MACRO database, which restrict access to their own particular role and site.

Data collected during the course of the research will be kept strictly confidential and accessed only by members of the trial team. Participant’s details will be stored on a secure database under the guidelines of the Data Protection Act 1998 and the General Data Protection Regulation (GDPR) from 25 May 2018. Participants will be allocated a unique trial number at randomisation which will be used on all study-related forms and questionnaires throughout the duration of the study. This will also allow anonymised versions of the secure database to be available to the trial team and subsequently processed for archiving. Personal data will not be kept for longer than is necessary for the purpose for which it has been acquired.

### Discontinuation rules

Data will be analysed at the end of the study; there are no planned interim analyses. An independent Data Monitoring Committee (DMC) will be convened to undertake independent review. The purpose of this committee will be to monitor efficacy and safety endpoints and will operate according to a written terms of reference linked to the DAMOCLES Charter. Only the DMC will have access to full un-blinded study data, if requested, prior to completion of the trial. All analyses will follow a carefully documented Statistical Analysis Plan (SAP). The DMC will be asked to review and comment on this plan prior to analysis. A single main analysis will be performed at the end of the trial when all follow-up has been completed. The DMC will meet initially to agree terms of reference and other procedures. The final trial report will contain full detail of the analytical methodology. The DMC will meet at least three times, at the start, middle and completion of the study. At the first meeting, the Committee will agree on its charter of operation, and discuss and advise on the inclusion of an interim analysis and possible adoption of a formal stopping rule for efficacy or safety.

### Assessment of study adherence

Some participants or their clinicians will seek to change their allocated group at some point during trial participation either due to lack of efficacy or adverse effects for either treatment. Trial literature will emphasise the need to adhere to the allocated strategy during the 12-month trial period if possible and will record any deviation. Multiple switching between prophylactic antibiotic agents will be allowed. If participants do stop their allocated treatment within the 12-month treatment period or if they re-commence prophylaxis during the subsequent 6-month observation period this will be recorded and the participant will continue on study unless they withdraw consent.

### Sample size calculation

The clinical trial has a planned recruitment target of 240 patients, 120 in each of the treatment arms. If there is an actual difference of 0.6 episodes (in favour of treatment with antibiotics), then two groups of 87 patients are required to be 90% sure that the lower limit of a one-sided 95% confidence interval (or equivalently a 90% two-sided confidence interval) will be above the non-inferiority limit of one UTI episode assuming a standard deviation of 0.9 episodes per year. Total sample size assuming two groups and an attrition rate of 25% = 232, rounded up to 240.

We have discussed extensively the relative merits of non-inferiority against superiority comparison and believe the key issue is that an orally administered urinary antiseptic would be acceptable to the patient group provided that their effectiveness for UTI prevention is no worse than antibiotic prophylaxis and that the burden of adverse effects is similar or better. There is also the key added potential benefit of reduced rates of resistant organisms and subsequent collateral harm to the individual and the community. The sample size calculation is based on the following assumptions:Semi-structured interviews with a patient panel of 12 women identified that any reduction in UTI episodes even by one per year would be deemed worthwhile. Therefore, we have set the minimum clinically important difference between the treatment arms of one UTI per 12 months as our non-inferiority marginThe two existing meta-analyses of studies examining prophylactic antibiotics [6] and methenamine hippurate [7] have quoted mean relative risk of UTI vs placebo of 0.15 and 0.24, respectively. Using these values and data from a local audit (unpublished, *n* = 200) suggesting that the average number of UTI episodes per year in this patient group is 6.5, we have estimated that the difference in number of episodes per year between prophylactic antibiotics and methenamine hippurate to be 0.6 episodes (in favour of antibiotics)The standard deviation of episodes of UTI per year is taken from the placebo groups in the studies included in the Cochrane meta-analyses [4, 10] and has been conservatively estimated at 0.9 episodes per yearThe type-1 error rate for a two group comparison is set at 5%, thus the calculation of a one-sided 95% confidence interval (or a two-sided 90% confidence interval)The attrition rate of participants in this study has been conservatively estimated at 25%

### Statistical analysis

The main analysis will comprise a comparison of patients randomised to antiseptic with patients randomised to antibiotic (‘intention to treat’).The primary clinical outcome is the occurrence of symptomatic UTI during the 12-month period of treatment. Our hypothesis is that treatment with antiseptic is not inferior to treatment with antibiotic. When considering an inferiority limit the variable that patients most readily relate to is the number of episodes experienced during treatment. The inferiority limit adopted for this study will be one episode per year. A 90% confidence interval for the difference between groups (antibiotic minus antiseptic) will be calculated using a resampling (bootstrap) procedure. Provided that the lower 90% confidence limit is greater than the pre-specified non-inferiority limit (here − 1 for this definition of difference as a higher (worse) value in the antiseptic group would result in a negative difference), we will infer that treatment with antiseptic is not inferior to treatment with antibiotic.

A secondary analysis of the primary outcome will involve the modelling of the number of episodes of UTI using a negative binomial regression model with differences between centre included as a random effect and a binary indicator of previous annual frequency of UTI at baseline (more than four episodes vs four or less episodes) and menopausal status (pre-menopausal vs menopausal/post-menopausal) will be included as fixed effects. This will yield an estimate of the incidence rate ratio. A binary indicator of at least one patient-reported or clinician-recorded symptom of UTI will be analysed using the same approach but with a binomial error structure. The same methods will be used to analyse the relative frequency of episodes of UTI during the 6-month post-treatment period as a secondary outcome.

Analysis of the secondary outcomes will follow a broadly similar strategy although non-inferiority will not be assessed as this is only relevant for the pre-specified primary outcome. Incidence or occurrence type outcomes will be analysed in a manner analogous to that previously described for the primary outcome. Patient satisfaction will be compared between arms using an analysis of variance/covariance approach adjusting for stratification variables and other predefined baseline covariates. Health-related QoL will be analysed as part of the health economics analysis.

We will also undertake a per-protocol analysis. The primary analysis will be repeated but on the subset of patients who have been treated in accordance with the treatment protocol for the arm to which they were randomised. Patients who switch treatments will still be analysed within the group to which they were randomised but only if that switching has been undertaken in accordance with the specified protocol.

A full SAP will be produced and finalised prior to data lock and analysis commencing.

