### Randomisation

Randomisation will be administered centrally by the Newcastle Clinical Trials Unit (CTU) secure web-based system. Permuted random blocks of variable length will be used to allocate participants 1:1 to the antibiotic and antiseptic groups. An individual not otherwise involved with the study will produce the final randomisation schedule. Stratification by two variables; prior frequency of UTI (less than four episodes per year or more than four episodes per year), and menopausal status of participants (pre-menopausal or menopausal/post-menopausal) will be performed prior to randomisation to ensure balanced allocation within these factors.

Following randomisation an appointment will be arranged, facilitated by trial staff, with the prescribing clinician to commence allocated treatment and ensure continued supply for the 12-month treatment period usually through hospital prescription or via the participant’s GP. The antibiotic selected for use as prophylaxis will be chosen by the patient and clinician with regard to individual participant characteristics, local guidance and standardised trial information with preferred agents being: nitrofurantoin first, trimethoprim second, cefalexin third.

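### The primary non-inferiority interval, as described, uses neither stratification factor; if the factors are prognostic it is mildly conservative and forgoes a modest gain in power

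*Protocol article*

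**What the plan says.** **Primary analysis** (Statistical analysis): "A 90% confidence interval for the difference between groups (antibiotic minus antiseptic) will be calculated using a resampling (bootstrap) procedure". Non-inferiority is inferred if the lower limit lies above −1 episode per year. No covariate or stratum is named, and the section does not say whether resampling is done within strata.

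**Secondary analysis** (same section): "A secondary analysis of the primary outcome will involve the modelling of the number of episodes of UTI using a negative binomial regression model". Centre is a random effect, and the fixed effects are "a binary indicator of previous annual frequency of UTI at baseline (more than four episodes vs four or less episodes) and menopausal status". The result is an incidence rate ratio.

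**Randomisation**: "Stratification by two variables; prior frequency of UTI (less than four episodes per year or more than four episodes per year), and menopausal status", which "will be performed prior to randomisation to ensure balanced allocation within these factors". Source of bias gives the reason: "to ensure equivalent proportions of these groups at differential risk in both arms".

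**Sample size calculation**: "two groups of 87 patients are required to be 90% sure that the lower limit of a one-sided 95% confidence interval" lies above the limit. The calculation uses a standard deviation of 0.9 and a true difference of 0.6 episodes, with no reduction for covariates.

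A full SAP is promised before data lock.

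**The concern.** Stratified randomisation removes most chance imbalance in the strata, so the treatment difference varies less from trial to trial. A crude bootstrap within each arm lets the stratum mix vary from draw to draw, and so puts that variation back. If the strata predict outcome, the estimated standard error is then larger than the true one, and the lower limit sits further from zero than it should.

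In this trial the lower limit is the decision. The protocol itself describes the strata as differing in risk, yet no analysis it describes uses them on the scale of the margin. What is at stake is precision that the design has already paid for.

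**Working it through.** **1. The plan's own figure.** With margin 1, true difference 0.6, SD 0.9, one-sided 5% and 90% power:

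n per arm = 2 × [0.9 × (1.645 + 1.282) / (1 − 0.6)]² = 86.7, rounded up to 87. Then 174 / 0.75 = 232, rounded up to 240.

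This matches the protocol. Power is 90.1% at 87 per arm and 90.9% at 90 per arm (240 less 25%). Nothing in the calculation relies on adjustment.

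**2. Formulas.** Let V_W be the sum over the two arms of the within-stratum variance, V_B the sum of the between-stratum variance, and n the number per arm. With strata balanced by design:

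- true SE of the difference: S_a = √(V_W / n), which a stratum-wise analysis also estimates
- SE reported by a crude analysis: S_u = √((V_W + V_B) / n)
- power, crude: Φ((δ − 1.645 S_u) / S_a)
- power, stratum-wise: Φ((δ − 1.645 S_a) / S_a)
- coverage of the crude 90% interval: 2Φ(1.645 S_u / S_a) − 1

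Here δ is the distance from the true difference to the margin.

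**3. On the plan's SD of 0.9** (87 per arm, δ = 0.4). The protocol does not give R², the share of outcome variance that the factors explain, so it is varied:

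| R² | Interval half-width, crude / adjusted | Power, crude / adjusted | Crude coverage |
|---|---|---|---|
| 0 | 0.224 / 0.224 | 90.1% / 90.1% | 90.0% |
| 0.05 | 0.224 / 0.219 | 90.7% / 91.3% | 90.9% |
| 0.10 | 0.224 / 0.213 | 91.2% / 92.6% | 91.7% |
| 0.20 | 0.224 / 0.201 | 92.5% / 94.9% | 93.4% |

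A bootstrap simulation (2,000 trials, 500 draws, one balanced binary stratum) agrees. Crude against stratum-wise power was 91.2% v 92.7% at R² 0.10 and 92.5% v 95.3% at R² 0.20, and crude coverage was 91.1% and 92.8%. The stratum-wise percentile interval covered 88.7% and 88.8%, with simulation error of about 0.7 points, so it may run slightly narrow.

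**4. On count data.** From Sample size calculation, the arm means are 6.5 × 0.15 = 0.975 and 6.5 × 0.24 = 1.56, so δ = 1 − 0.585 = 0.415. With 90 per arm, the assumptions are the rate ratio between high and low stratum, the share of women in the high stratum, and the negative binomial dispersion k (k = 0 is Poisson). Within-stratum variance is μ + kμ².

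| k | High-stratum share | Rate ratio | S_u / S_a | Power, crude / stratum-wise | Crude coverage |
|---|---|---|---|---|---|
| 0.3 | 50% | 1.5 | 0.203 / 0.200 | 65.6% / 66.7% | 90.6% |
| 0.3 | 50% | 2 | 0.212 / 0.202 | 62.9% / 66.0% | 91.6% |
| 0.3 | 50% | 3 | 0.227 / 0.206 | 57.9% / 64.6% | 93.1% |
| 0.3 | 80% | 2 | 0.205 / 0.200 | 65.3% / 66.6% | 90.8% |
| 0.3 | 80% | 3 | 0.210 / 0.201 | 63.5% / 66.2% | 91.4% |
| 0 | 50% | 2 | 0.180 / 0.168 | 76.1% / 79.6% | 92.2% |
| 0 | 50% | 3 | 0.194 / 0.168 | 71.7% / 79.6% | 94.3% |

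Simulating stratified trials at k = 0.3 and a 50:50 split (4,000 per scenario) gives 65.0% / 66.2%, 63.4% / 66.2% and 57.6% / 63.8% for ratios of 1.5, 2 and 3, with crude coverage of 90.5%, 90.9% and 92.5%.

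**5. Type I error.** With the true difference at the margin, the crude rule wrongly declares non-inferiority with probability Φ(−1.645 S_u / S_a). In the last row this is Φ(−1.645 × 0.194 / 0.168) = 2.9%, and it never exceeds 5%.

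**6. The stratum definition.** Randomisation contrasts fewer than four episodes with more than four, leaving exactly four unplaced. Source of bias contrasts more than four with four or more, which overlap. Statistical analysis contrasts more than four with four or fewer. Only the last pair divides all women into two groups.

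**The case against.** The protocol never calls the bootstrap unadjusted. The form of the resampling is commonly left to a SAP, and one is promised. That stands as a caution: the unseen SAP may already resample within strata. Against it, the section names adjustment wherever it is intended, including for patient satisfaction, and labels the adjusted model of the primary outcome as secondary.

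A reader might infer that the trial therefore falls short of its stated power. The documents do not support that: 90% was computed for an unadjusted comparison with SD 0.9, and step 1 reproduces it. The power figures between 58% and 80% in step 4 arise mainly because count variances at the assumed arm means exceed 0.9². That is a separate question about the SD. Only the gap between the two power columns belongs to this point.

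The size is also fairly contested. The rate ratios, dispersion and split are all assumed. With a mean of 6.5 episodes and a cut near four, the high stratum may well hold most women, which shrinks the gain. A crude difference on the margin's own scale, backed by an adjusted model, is a defensible choice.

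**Conclusion.** The point holds as a matter of efficiency. As described, the decisive interval uses neither stratification factor, and the analysis that does use them is on a scale the margin cannot be applied to. If the factors are prognostic, as the protocol implies, the crude interval covers about 90 to 94% instead of 90%. The power forgone is about 1 point at a rate ratio of 1.5, 3 to 4 at 2, and 6 to 8 at 3 with an even split. With 80% of women in the high stratum it is about 1 to 3 points. If the factors are not prognostic, nothing is lost.

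Two stronger readings fail. The error is in the conservative direction, so it does not raise the risk of falsely declaring non-inferiority. And what is lost is an available gain, with no shortfall against the planned power. A reader might also expect more from using the baseline UTI count as a continuous covariate. That gain has not been calculated, and the protocol does not say that a count is recorded.

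**What to change.** Before data lock, in this order:

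1. Reconcile the UTI-frequency cut-point across Randomisation, Source of bias and Statistical analysis, stating where a woman with exactly four episodes falls and which definition the randomisation system used.
2. Define the primary estimate as the difference in UTI rate (antibiotic minus antiseptic), adjusted for or standardised over the two factors as randomised. Marginal predictions from the negative binomial model already planned would serve. State how centre is handled.
3. Take the 90% limit from a bootstrap within arm and stratum. Name the interval type and check its coverage by simulation, since the percentile form ran slightly narrow in step 3 and two binary factors in two arms give eight cells.
4. Keep the crude difference as a sensitivity analysis. Leave the margin and decision rule unchanged.
5. Use the baseline UTI count in place of the binary indicator only if it is recorded.

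The cost is some SAP text, a little code and modest reliance on a model. Steps 1 to 4 need no new data or participants.
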